## Abstract

**Background:**

Bronchiolitis is the most common reason for admission of infants to hospital in developed countries. Fluid replacement therapy is required in about 30% of children admitted with bronchiolitis. There are currently two techniques of fluid replacement therapy that are used with the same frequency-intravenous (IV) or nasogastric (NG).

The evidence to determine the optimum route of hydration therapy for infants with bronchiolitis is inadequate. This randomised trial will be the first to provide good quality evidence of whether nasogastric rehydration (NGR) offers benefits over intravenous rehydration (IVR) using the clinically relevant continuous outcome measure of duration of hospital admission.

**Methods/Design:**

A prospective randomised multi-centre trial in Australia and New Zealand where children between 2 and 12 months of age with bronchiolitis, needing non oral fluid replacement, are randomised to receive either intravenous (IV) or nasogastric (NG) rehydration.

750 patients admitted to participating hospitals will be recruited, and will be followed daily during the admission and by telephone 1 week after discharge. Patients with chronic respiratory, cardiac, or neurological disease; choanal atresia; needing IV fluid resuscitation; needing an IV for other reasons, and those requiring CPAP or ventilation are excluded.

The primary endpoint is duration of hospital admission. Secondary outcomes are complications, need for ICU admission, parental satisfaction, and an economic evaluation. Results will be analysed using t-test for continuous data, and chi squared for categorical data. Non parametric data will be log transformed.

**Discussion:**

This trial will define the role of NGR and IVR in bronchiolitis

**Trail registration:**

The trial is registered with the Australian and New Zealand Clinical Trials Registry - ACTRN12605000033640

## Background

Bronchiolitis is a disease of the lower respiratory tract with peak incidence in the winter. It is the leading cause of hospitalisation during the first year of life and is a major cause of morbidity and mortality [1-5]. Victorian state-wide data for the calendar year 2006 reveal 2280 admissions for bronchiolitis, with an average length of stay of 3.2 days. One hundred sixty eight (7.4%) patients were admitted to intensive care. The estimated cost of the Victorian bronchiolitis hospital admissions for 2006 is $8.1 million dollars (data supplied at personal request from Victorian Admitted Episodes Dataset, Performance Reporting & Analysis Unit, Department of Human Services Victoria). In the United States of America bronchiolitis accounts for 21% of all hospital admissions for children under 1 year of age, with an annual cost of $390 million dollars [5].

There are no clearly effective chemotherapeutic treatments to improve the outcome of infants with bronchiolitis, so treatment is limited to oxygen, supportive care of breathing, and fluid replacement therapy[1,2,6-10]. Maintaining hydration is an important component of the care of infants with bronchiolitis. Fluid replacement therapy is required in about 30% of children admitted with bronchiolitis, due to reduced oral intake and evaporative losses from increased respiratory effort and fever [11].

There are currently two techniques of fluid replacement therapy, IV or NG. There is a lack of agreement on which method of fluid replacement is most beneficial for patients with bronchiolitis - we do not know which therapy is better. They both have theoretical grounds for superiority, but both also have a range of possible complications. As fluid replacement is such an important aspect of the management of this common disease it is very important that fluid therapy is evidence based.

Nasogastric fluid replacement (NGR) is effective and has few complications. It provides the physiological benefit of enteral hydration, which allows the body to absorb the required amounts of water and solute. In children with dehydration due to gastroenteritis, NGR is the treatment of choice as it provides faster recovery, shorter hospital stay and lowers the cost compared to IV fluid replacement (IVR) [12,13]. A nasogastric tube (NGT) can often be inserted more easily than an IV catheter, especially in infants with poor peripheral circulation due to reduced oral intake. However, concerns have been raised regarding the use of nasogastric tubes (NGT) in infants with bronchiolitis. There may be an increased risk of aspiration in patients with bronchiolitis [14]. The partial obstruction of the upper airway may compromise respiratory function, [15-18] with some studies showing up to a 50% increase in the work of breathing [16]. However these studies have been mostly in young or preterm infants and the ability to extrapolate these findings to older infants with bronchiolitis is questionable.

Intravenous fluid replacement (IVR) is commonly used in bronchiolitis[1]. However, accidental water intoxication and electrolyte imbalances are potential complications [10]. Up to 30% of children admitted with bronchiolitis have been shown to have some degree of hyponatraemia requiring vigilance with IV fluid administration[19,20]. It has also been postulated that delaying enteral nutrition will cause delay in recovery due to loss of nutritional status, and that the persisting hunger may make the children more irritable.

Kennedy et al (2005)[21] reviewed the evidence for fluid replacement in children with bronchiolitis. The authors report a wide variation in practice, with use of NGR in many units. They conclude that "there is no good quality evidence for or against the use of NGR in infants with bronchiolitis. A randomised controlled trial is needed." Vogel (2003) [22] described the management of bronchiolitis admissions in New Zealand hospitals in 1998. There was a large variation in management between hospitals, with between 6% and 64% of children needing fluid replacement therapy receiving NGR.

We confirmed the wide variation of practice in Australia with a pilot study. As baseline data for our proposed study, a survey of Australasian paediatric emergency physicians was undertaken in 2005, by the Paediatric Research in Emergency Departments International Collaborative (PREDICT), a research collaborative of all tertiary paediatric emergency departments and major mixed emergency departments in Australia and New Zealand). Of the 78 senior doctors surveyed at 11 sites (including all tertiary paediatric emergency departments in Australia and New Zealand), 48% reported using NGR and 52% IVR as initial treatment in acute bronchiolitis. There were no guidelines in any institution to determine which fluid replacement therapy should be used in bronchiolitis [23].

There are no published trials directly comparing NGR and IVR. The research available on NGR in bronchiolitis comes from two small studies. In a case series of 37 infants with bronchiolitis, Sammartino (2002) [24] found NGR was tolerated without incident. Two infants deteriorated as the illness progressed and removal of the NGT did not help.

Smyth and Openshaw[10] in a *Lancet *review article conclude "Neither oxygen therapy, nor fluid replacement strategies have been validated in large randomised controlled trials, although the dangers of hyponatraemic fluid overload are recognised. These treatment options should be addressed in randomised controlled trials." Further Smyth states that "Clinical trials of interventions in bronchiolitis have been criticised for being too small and focusing on short-term outcomes, rather than reporting outcomes of interest to clinicians and parents, such as length of hospital stay."

Davison et al [6] conclude in another recent review: "There is an ongoing need for studies that are adequately powered to identify therapies that may benefit critically ill children with this disease (bronchiolitis). Because the mortality associated with bronchiolitis is low, large multicentre trials that focus on continuous outcome measures such as duration of mechanical ventilation and ICU or hospital length of stay will provide the best opportunity to demonstrate a clinical benefit with adequate statistical power."

The evidence to determine the optimum route of hydration therapy for infants with bronchiolitis is inadequate. This randomised trial will be the first to provide good quality evidence of whether NGR offers benefits over IVR.

## Methods/Design

### Study Aims

The primary aim of this multicentre randomised trial is to investigate whether the type of fluid replacement - NG versus IV - affects the duration of hospital admission, in children aged between 2 and 12 months admitted to hospital with a clinical diagnosis of bronchiolitis. Secondary aims are to undertake an economic appraisal, and to determine the difference in the incidence of complications, duration of treatment and parental satisfaction for the two treatments.

We hypothesise that there will be a difference in the length of hospital stay between the two treatment modalities.

### Study Design and setting

This study is an open randomised trial comparing two interventions. This study will take place in 6 paediatric emergency departments and inpatient wards in Australia and New Zealand.

### Ethical considerations

The study has ethical approvement at all participating sites. All parents/guardians are provided with both verbal and written information about the study and written informed consent is obtained prior to enrolment in the trial.

The trial is overseen by a trial steering committee that is responsible for the ethical and rigorous conduct of the trial.

A data monitoring committee (with membership entirely independent of the conduct of the trial) will monitor adverse events and review outcomes and complications annually. They will report and make recommendations to the trial steering committee. No formal stopping rules are in place.

### Subject Selection

Children satisfying the inclusion and exclusion criteria who are admitted to the hospital will be eligible for the study. Patients admitted to the ward with bronchiolitis who deteriorate and need institution of hydration will be eligible for randomisation. Figure 1 outlines the flow of patients through the study.

**Figure 1 F1:**
[figure not shown]
**Patient identification and entry into CRIB study**.

### Definition of Disease State

The eligible patients will be all children younger than 12 months and older than 8 weeks (corrected for prematurity) presenting to the Emergency Department with bronchiolitis requiring hydration. The need for hydration will be defined by a history of oral intake less than 50% in the last 6 hours or signs of dehydration such as reduced urine output, tachycardia (in the absence of fever), dry mucous membranes, decreased skin turgor or sunken fontanelle.

### Inclusion and Exclusion Criteria

Inclusion and exclusion criteria are shown in Additional File 1. In order to keep the study group as homogeneous as possible patients younger than 8 weeks were excluded as the very young often have a different and more severe clinical presentation and course of bronchiolitis. Children older than 12 months were also excluded as other diagnoses, in particular asthma assume an increasing role, impacting on the identification and management of these patients.

### Patient randomisation

The patients will be randomised at the time they require non oral fluid replacement. Randomisation will be stratified by 2 age groups (2 months to less than 6 months, 6 months to less than 12 months) and by site. Randomisation will be blocked in 3 randomly allocated block sizes to ensure concealment of allocation. Each site will have its own set of opaque sealed randomisation envelopes. These will have a reminder of inclusion and exclusion criteria to be assessed before the envelope is opened.

### Randomised treatments

#### Intravenous fluid replacement group

Topical anaesthetic cream will be used in accordance with hospital policy to reduce the pain of IV insertion. Insertion of the IV cannula will be at the site of anaesthetic cream application after 30-60 minutes. Size 22 or 24 gauge cannulae will be used for all cases. The fluid used for hydration will be 0.45% Sodium Chloride with 2.5 or 5% dextrose. Ongoing fluid replacement will be guided by the measured serum electrolytes (see "Data Collection").

#### Nasogastric fluid replacement group

Insertion of the NGT will be by experienced personnel. The nostril will be sprayed with local anaesthetic spray 2 minutes prior to NGT insertion. The tube will be measured from nares to epigastrium to determine depth of insertion. Post insertion correct tube placement will be confirmed by aspiration of stomach contents with pH < 4. Failed aspiration or pH ≥4 should be repeated after 30 minutes. A repeated failure to confirm the presence of the NGT in the stomach by these means requires an abdominal/chest x-ray to be performed to confirm the position of the tube prior to its use. If there is doubt about the position of the tube after this it should be removed and replaced. Tubes will be size: 6 French < 6 months of age, and 8 French 6-12 months of age. NGR will be by continuous infusion with a standard oral electrolyte solution for the first two hours, followed by expressed breast milk or formula.

##### For both groups

All patients will be admitted to the ward under the appropriate unit. Total fluid replacement will not exceed 100% of normal daily requirements. Oral feeds will be at the discretion of the clinical team and the IV or NG fluid rate adjusted accordingly.

A parent satisfaction score will be obtained using a standardised, five point Likert scale. The score will be obtained daily from one parent or by agreement with both parents if they are in attendance. A final "overall" satisfaction score will be obtained immediately prior to hospital discharge.

All patients will be followed up at 5 to 7 days post discharge with a standard questionnaire to determine the incidence of complications, or need for further medical care.

### Study Procedure

All patients will have all clinical observations entered into a Clinical Report Form (CRF) by the nursing staff at the time of performing the observations. All CRFs will be checked daily by research staff while the participant is an inpatient.

#### Clinical observations from nursing records

SpO_2_, respiratory rate, respiratory effort, and heart rate will be measured at enrolment, at hourly intervals for the first 2 hours then 2 hourly. These will allow comparison of groups by severity of disease at enrolment, and ensure any clinically relevant complications are captured.

Oxygen administered (L/min for nasal cannulae or %O_2 _for head box) will be documented for each shift. The times oxygen is commenced and ceased will be documented. This will allow accurate capture of the duration of oxygen therapy. Type, route and volume of fluid administered will be recorded, with hourly, shift, and daily totals. This allows assessment of fluid requirements and cross referencing volumes of fluid infused. Hydration status of the patients will be measured using urine output (with shift and daily totals) and weight (measured at the time of admission, and then daily).

Complications recorded will include: episodes of apnoea and bradycardia (lasting more than 20 seconds); all episodes where the SpO_2 _was recorded at < 90%; and the need for replacement of, or problems with the IV cannula or NGT.

The need for and duration of ICU admission will be documented. Duration of hospital admission will be documented and checked by calculation from the hospital admissions and discharge system.

#### Laboratory investigations

Electrolytes, urea and creatinine, and glucose levels will be measured when inserting the IV line. Electrolytes will be repeated 6-8 hours after commencement of therapy in the intravenous therapy group (as an accepted standard in IV fluid management); and daily thereafter. Blood sampling may be by draw back on IV cannulae with discarding of 2 mls of blood or alternatively sampling by IV access or capillary blood sample at the discretion of physician managing patient. All testing of electrolyte levels in patients with iv fluids and non testing in patients with NG fluids are in line with current local recommended practice and represent standard care at the participating hospitals [23]. No additional blood tests will taken for the purpose of this trial.

Other investigations will be at the discretion of the managing physician.

#### Post discharge phone review

Will be undertaken for all patients 5 to 7 days post discharge. Information collected will include return visits to a hospital, admission to hospital, attendance at local medical officer - planned and unplanned and other complications including difficulty feeding, nasal sores, arm bruising or sores.

### Guidelines for oxygen therapy

• Oxygen should be commenced to keep SpO2 ≥ 92%, or if there is markedly increased work of breathing and respiratory distress.

• The least amount of oxygen needed to keep SpO2 ≥ 92% should be administered.

• Oxygen should be ceased when SpO2 is consistently above 92%, and the child is able to feed well. Cease by weaning the flow as tolerated until 1 l/min or less is needed.

Guidelines for non-oral fluid commencement are presented in Table 1.

**Table 1 T1:** Guidelines for commencement of non oral fluid therapy.

Weight (Kg)	Fluid rate (mls/hr)	
	**Intravenous**	**Nasogastric**

3.0	10	12
4.0	13	18
5.0	16	21
6.0	19	24
7.0	22	27
8.0	26	30
9.0	29	33
10	32	36
12	35	39
15	40	42
20	48	50

**Note: **total initial hydration rate is determined at about 80% maintenance fluid requirements, and should never exceed 100% of daily fluid requirements

Guidelines for changing the treatment from one intervention to the other are presented in Additional File 2.

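### Table 1 gives one target of about 80% of maintenance for both routes, but at low weights its NG and IV starting rates differ too much for both to meet it

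*Protocol article*

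**What the plan says.** Table 1 of the protocol article stands in the section *Guidelines for oxygen therapy* and is titled "Guidelines for commencement of non oral fluid therapy". It has eleven weight rows from 3 to 20 kg, with one column of hourly rates for IV and one for NG. The NG figure is the higher in every row. A single note beneath the table, not divided by route, says: "total initial hydration rate is determined at about 80% maintenance fluid requirements, and should never exceed 100% of daily fluid requirements".

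The upper limit appears again in the section *For both groups*: "Total fluid replacement will not exceed 100% of normal daily requirements". That section also lets the clinical team allow oral feeds and adjust the IV or NG rate to them. The article gives no maintenance formula, no separate NG target and no reason for the difference between the columns.

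**The concern.** The note treats the table as one schedule set at one fraction of maintenance. Maintenance, as the note uses it, depends on the infant and not on the route. Two clearly different rates at the same weight therefore cannot both sit near the same fraction. If the lower rate is the one near 80%, the higher one may pass the protocol's own limit.

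Two things are at stake. Staff start infants from this table, and a starting rate should not be open to conflict with a limit that the protocol states twice. The arms may also differ in starting volume without the protocol saying that this is meant, so a reader of the results would not know whether a volume difference was planned.

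**Working it through.** **Inputs.** All rates are from Table 1, in mL/h. The target (about 80%) and the cap (100%) are from its note; the cap is also in *For both groups*.

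**The plan's own figure.** The 80% cannot be reproduced directly, because the article gives no maintenance formula. The ratio of the columns can be checked without one. Let M be the requirement at a given weight. Then IV% = 100 × IV / M and NG% = 100 × NG / M, so NG% / IV% = NG / IV, and M cancels.

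**Three ways to fit M.**
- IV column at 80%: M = IV / 0.8, so NG% = 80 × NG / IV.
- NG column at 80%: M = NG / 0.8, so IV% = 80 × IV / NG.
- The columns placed evenly around 80%: M = ((IV + NG) / 2) / 0.8.

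At 4 kg:
- IV at 80%: M = 13 / 0.8 = 16.25 mL/h, and NG is 18 / 16.25 = 110.8%.
- NG at 80%: M = 18 / 0.8 = 22.5 mL/h, and IV is 13 / 22.5 = 57.8%.
- Even split: M = 15.5 / 0.8 = 19.375 mL/h, and IV / NG are 67.1% / 92.9%.

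| Weight (kg) | IV | NG | NG / IV | NG% if IV is 80% | IV% if NG is 80% | Even split, IV% / NG% |
|---|---|---|---|---|---|---|
| 3 | 10 | 12 | 1.20 | 96.0 | 66.7 | 72.7 / 87.3 |
| 4 | 13 | 18 | 1.38 | 110.8 | 57.8 | 67.1 / 92.9 |
| 5 | 16 | 21 | 1.31 | 105.0 | 61.0 | 69.2 / 90.8 |
| 6 | 19 | 24 | 1.26 | 101.1 | 63.3 | 70.7 / 89.3 |
| 7 | 22 | 27 | 1.23 | 98.2 | 65.2 | 71.8 / 88.2 |
| 8 | 26 | 30 | 1.15 | 92.3 | 69.3 | 74.3 / 85.7 |
| 9 | 29 | 33 | 1.14 | 91.0 | 70.3 | 74.8 / 85.2 |
| 10 | 32 | 36 | 1.13 | 90.0 | 71.1 | 75.3 / 84.7 |
| 12 | 35 | 39 | 1.11 | 89.1 | 71.8 | 75.7 / 84.3 |
| 15 | 40 | 42 | 1.05 | 84.0 | 76.2 | 78.0 / 82.0 |
| 20 | 48 | 50 | 1.04 | 83.3 | 76.8 | 78.4 / 81.6 |

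**When NG stays within the cap.** NG% is at most 100 only if IV% is at most 100 × IV / NG. This gives 72.2% at 4 kg (13 / 18), 76.2% at 5 kg (16 / 21) and 79.2% at 6 kg (19 / 24).

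**Rounding.** Suppose each printed rate is rounded to the nearest mL/h and IV is at 80%. NG% then runs from 80 × (NG − 0.5) / (IV + 0.5) to 80 × (NG + 0.5) / (IV − 0.5):
- 4 kg: 103.7% to 118.4%, above the cap throughout.
- 5 kg: 99.4% to 111.0%, above it over nearly the whole range.
- 6 kg: 96.4% to 105.9%, on both sides of it.

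**Dependence on the unknown formula.** The article gives no requirement per kg, so these values are assumptions, applied to 3–10 kg only.

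| Assumed requirement (mL/kg/h) | IV% | NG% | NG above 100% |
|---|---|---|---|
| 3.5 | 90–95 | 102.9–128.6 | every row |
| 4.0 | 79–83 | 90.0–112.5 | 4 and 5 kg |
| 4.5 | 70–74 | 80.0–100.0 | none |
| 5.0 | 63–67 | 72.0–90.0 | none |

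Whether the cap is passed depends on the value assumed. The gap between the columns does not.

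**The case against.** The strongest reply is that the schedule may be deliberate. NG is higher in all eleven rows under its own column heading, which fits an intended difference by route with a loosely worded note. The article may also have left the maintenance formula to a fuller document. Both are possible, and they are why the cap conflict can only be stated conditionally. Neither rescues the note, which gives one target for the whole table.

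A second reply is that these are starting rates, that the cap under *For both groups* overrides them, and that rates are adjusted for oral feeds. That lowers the practical risk, but it does not make the printed rates agree with the printed target.

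A reader might also go further in four ways that the documents do not support:
- **That the table is shown to break the cap at 4, 5 and 6 kg.** This needs IV fixed at 80%, whereas the note says only about 80%. Even then, 6 kg is within rounding.
- **That the smallest infants are the ones affected.** With IV at 80%, the lightest row, 3 kg, is at 96.0%.
- **That there is an entry error.** The NG column rises by 6 mL/h from 3 to 4 kg and then by 3 mL/h per kg up to 10 kg. One wrong entry at 3 kg would not explain the conflict at 4 to 6 kg, which lies in the regular part of the column.
- **That the volume difference undermines the comparison of routes.** The arms already differ in the fluid given (saline with dextrose, against electrolyte solution and then milk feeds), and *Limitations* describes a real-world comparison. Volume can be one more component of each strategy, and the randomised comparison of the two remains valid.

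**Conclusion.** The point holds as an internal contradiction. At 4 to 7 kg the NG starting rate is 38%, 31%, 26% and 23% above the IV rate, and no single requirement puts both columns at about 80%. The conflict is plainest at 4 to 6 kg. From 8 kg the gap is 15% or less and shrinks to 4% at 20 kg, so at the higher weights both columns can fairly be called about 80%. This rests on one assumption: one maintenance requirement per weight for both routes, which is how the undivided note reads.

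The conflict with the 100% cap is conditional on the IV column being the one at 80%. On that reading NG is 110.8% at 4 kg (robust to rounding), 105.0% at 5 kg (nearly so) and 101.1% at 6 kg (within rounding). At 4 kg it disappears if IV is 72% of maintenance or less, but IV is then about 8 percentage points or more below the stated target.

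The passages must be reconciled because infants are started from this table and the limit is a safety rule stated twice. Which rate, target or limit is right is a clinical matter on which no view is given.

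**What to change.** The clinical leads should reconcile three items: the rates in Table 1, the note beneath it, and the cap under *For both groups*. They should then issue one consistent table to all sites, with the maintenance requirement behind it stated so that the percentages can be checked.

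If a difference in volume by route is intended, the note should say so in place of the single target. Delivered volume in mL/kg/h should then be reported by arm. *Clinical observations from nursing records* already provides for type, route and volume of fluid with hourly, shift and daily totals, and for weight at admission and daily, so no new data are needed.

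The cost is a corrected table, a notice to sites and one descriptive tabulation. The *Discussion* reports just over 190 infants randomised out of a planned 750, so at that point most would still be started from the reconciled table.
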